##### Training adherence

The frequency of addressed practice behavior during the last month before assessment is recorded. Participants report how often per week and how long per session (minutes) they perform memory or relaxation/mindfulness exercises. Two training scores (in minutes per week) are calculated by multiplying the number of sessions by minutes per session. In addition, they are asked how often per week and how long per session they perform strenuous, moderate, and light physical exercise outside of work duties (adapted version of the Godin Leisure-Time Exercise Questionnaire; [40]). A total physical activity score (in minutes per week) is calculated by multiplying the total number of sessions per week in each domain by the minutes per session in each domain. For each of the scores, higher scores indicate a higher level of training adherence.

##### Treatment satisfaction

Participants are asked to judge the MPMI using 22 items. Patients were asked to judge the structure (e.g., duration, group size, online setting; 4 items) and implementation (e.g., content, exchange of experience, booklet; 6 items) on a 6-point scale (1 = very good; 6 = insufficient). Furthermore, the usefulness of the program is rated with four items (i.e., theoretical content, group interaction, psychomotor exercises, and memory exercises) on a 4-point scale (1 = is completely true; 4 = does not apply at all). In addition, two items inquire about training performance (memory exercises, psychomotor exercises) outside the sessions on a 5-point scale ranging from “daily” (1) to “never” (5). Furthermore, four items address the general satisfaction with the program (e.g., recommending the training to others) on a 4-point scale (1 = absolutely; 4 = in no case). Lower scores correspond to higher satisfaction and training performance, respectively. Finally, participants can give feedback on the most helpful aspects and make suggestions using two items with an open response format.

### Participant timeline

Figure 1 presents the SPIRIT schedule of enrollment process, intervention, and assessments performed on participants.

**Fig. 1 Fig1:**
[figure not shown]
SPIRIT schedule of enrollment, interventions, and assessments

### Sample size

The primary outcome is the change in the alertness as reaction time in milliseconds (without critical stimulus/warning signal) during the intervention (t1–t2). Based on data from a neuropsychological training in a rehab setting [41], a mean difference of 16 ms (SD = 46.5) between the intervention and control group was estimated.

Therefore, sample size was powered to detect a significant difference of 16 ms (SD = 46.5) in the primary outcome between the study groups (2-sided* α* = 0.05, 1−*β* = 0.80) using analysis of covariance (ANCOVA) and adjusting for baseline values. We assumed a *R*^2^ of 0.5 for the regression of the response on only the baseline covariate. Thus, a total of *n* = 136 persons (*n* = 68 per group) is required. We will include *n* = 170 patients (*n* = 85 per group) based on an estimated dropout rate of 20%.

Furthermore, medium between-group effects (*d* = 0.48) on secondary outcomes can be detected (*p* < 0.05, 1− *β* = 0.80). As power to detect smaller between-group effects on secondary outcomes may be lacking, effect sizes and accompanying 95% confidence intervals will be reported throughout. Sample size calculation was conducted in Power Analysis & Sample Size PASS 2020 (NCSS, LLC, Kaysville, Utah; https://www.ncss.com/software/pass) by a statistician from the Institute of Clinical Epidemiology, University of Würzburg.

### Recruitment

Recruitment is based on the ONKOSTAR tumor documentation system (T-Choice software). A filter is applied to identify people between the ages of 18 and 80 years with an eligible diagnosis. Subsequently, a researcher checks the inclusion and exclusion criteria in the electronic patient file. After screening, potential participants are contacted and informed about the study via phone. Persons interested in the study receive the study information by mail. After signing the informed consent form and completing the FACT-Cog online, participants with a PCI18 score of ≤ 55 (cut-off value representing self-reported cognitive impairment) are included.

In addition to the electronically selected patients, members of the psycho-oncological team of the CCCMF can recommend patients for the study. Furthermore, interested patients can contact the MPMI team after being drawn to attention by MPMI flyers distributed at the oncological departments and the hospital homepage.

## Assignment of interventions

### Randomization and allocation concealment

All participants are randomly assigned to the IG or CG after consent is given and initial assessment and questionnaires (t1) are completed. A block randomization procedure (block size: 2 and 4) with an allocation ratio of 1:1 is used. A member of the Institute of Clinical Epidemiology and Biometry at the University of Würzburg (external randomization) created for each of the eight-session groups a separate randomization list with computer-generated random numbers, which is stored locked at the IKE-B.

Members of the research team are informed about the allocation after the baseline assessment. Therefore, a consecutive list with the participants’ IDs (research codes) of each session group is sent per e-mail to the IKE-B member. Randomization results are added to the IDs and sent back per e-mail afterwards.

### Blinding

Blinding of participants and therapists is impossible due to the nature of the intervention (active training group) and waiting control condition. Further care providers are blind to study participation and/or assignment. Furthermore, assessors are blind to treatment allocation at baseline assessment. For organizational reasons, they cannot be blinded by follow-up assessments. Two clinical research associates must take on several tasks and are responsible for enrollment, data collection and management, and intervention implementation.

A research assistant at the Institute of Clinical Epidemiology and Biometry at the University of Würzburg will perform statistical analysis. Therefore, an external researcher can analyze data and prove intervention effects (main research question).

## Data collection, data management, and confidentiality

After inclusion in the study, medical data are extracted from the electronic patient file. Outcomes and other parameters are assessed using online questionnaires and cognitive and functional performance tests at t1 to t3. The assessments are conducted in the CCCMF using a standardized case report form (CRF). Participants receive a link to the online questionnaires 1 week before the data collection appointment in the clinic. These can be completed within 6 days via an online platform (Evasys GmbH). Researchers contact non-responders by e-mail or phone to ensure completion.

All data are transferred to Microsoft Excel (2016) and stored on secured servers with regular backup. Test sheets are stored in locked cabinets. Only the members of the research team have access to the data. Double data entries are processed for 20% of the manually transferred data (test data, medical data) to assess data quality. Moreover, range checks for data values are performed.

All data are pseudonymized to ensure confidentiality. For this purpose, each study participant is assigned a research code. The password-protected code list (including name, date of birth, SAP research number, and contact data) is stored locked on a server and file folder that is inaccessible to the public. It is accessible only to the research members responsible for the assignment and data collection.

The principal investigator will retain all collected data for at least 10 years. At the end of the study, the code list will be deleted.

### Statistical analysis

Statistical analysis will be performed using R 4.5.1 (R Foundation; https://www.r-project.org/), SAS 9.4 (SAS Campus Drive, Cary, NC, USA), and SPSS (IBM Corp, Armonk, NY, USA) version 29 Statistics for Windows. Depending on missing data analysis, missing data for outcome variables in accordance with missing completely at random (MCAR) or missing at random (MAR) assumptions will be imputed using a multiple imputation procedure. In addition, missing values due to drop-out or data not missing at random (NMAR) will be analyzed by pair-wise deletion. Drop-out analyses will be carried out by independent group comparisons using t-tests for continuous variables and chi-square tests for categorical variables. Descriptive analyses will be performed concerning socio-demographic and medical data.

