#### Main research question

The primary and secondary endpoints will be analyzed according to the intention-to-treat principle. Treatment effects (between-group effects) will be calculated separately for each follow-up time point using analysis of covariance (ANCOVA) adjusting for baseline values. Statistical significance (*p* < 0.05, two-sided), difference in means with 95% confidence intervals (CI), and effect sizes (ή^2^) will be reported for all outcomes. Furthermore, within-group effects, including standardized effect sizes (SES) and accompanying 95% CI, will be calculated for both study groups. Bonferroni corrections to adjust the significance level for multiple tests are planned within secondary cognitive outcomes. Further secondary outcomes will be analyzed exploratorily without adjustment. A sensitivity analysis is conducted for primary analysis by additionally including the group as random effects in a linear mixed model for the primary endpoint to estimate the effect of the group.

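### Drop-outs and not-at-random values are deleted pair-wise, which conflicts with the intention-to-treat statement and can bias the primary comparison

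*Protocol article*

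**What the plan says.** The Protocol article, Statistical analysis, gives two rules for missing outcomes. Depending on an analysis of the missing data, values judged missing completely at random (MCAR) or at random (MAR) "assumptions will be imputed using a multiple imputation procedure". The next sentence takes a different line for the rest: "missing values due to drop-out or data not missing at random (NMAR) will be analyzed by pair-wise deletion". Group comparisons of drop-outs by t-test and chi-square test are also planned.

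Under the Main research question heading of the same section, the article states: "The primary and secondary endpoints will be analyzed according to the intention-to-treat principle". Treatment effects are estimated "separately for each follow-up time point using analysis of covariance (ANCOVA) adjusting for baseline values". One sensitivity analysis is named for the primary endpoint: "A sensitivity analysis is conducted for primary analysis by additionally including the group as random effects in a linear mixed model". It does not concern missing data.

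The Sample size section needs 136 patients and enrols 170, "based on an estimated dropout rate of 20" per cent.

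**The concern.** Drop-out is the only source of missing outcomes that the article quantifies, and the imputation rule excludes it. Four difficulties follow from the text.

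- **Conflict with intention to treat.** Patients without a follow-up value leave the comparison, although the endpoints are said to be analysed by intention to treat.
- **Two rules for the same patient.** Drop-out is a reason for missingness, whereas MAR and not missing at random (NMAR) are mechanisms. A drop-out whose missingness is MAR falls under both sentences, which prescribe opposite handling.
- **A trigger that cannot work.** Observed data cannot separate MAR from NMAR, so the choice of method, and with it the analysed set, rests on a judgement made after the data are in.
- **Deletion where it is least defensible.** NMAR values are assigned to deletion, and no sensitivity analysis tests the consequence for the primary endpoint.

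At stake is the primary comparison. Participants are not blinded (Blinding section), and controls may take the training only after the last follow-up (CG section). Reasons for being lost could therefore differ between the arms.

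**Working it through.** **Inputs.** From Sample size: difference 16 ms, SD 46.5, R² 0.5 for the baseline covariate, two-sided alpha 0.05, power 0.80, drop-out 20%. From Main research question: a separate baseline-adjusted ANCOVA at t2 and at t3. The drop-out mechanisms below are assumptions, because the article gives none.

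**1. The plan's own figure.** Residual variance = 46.5² × (1 − 0.5) = 1081.1. The normal approximation gives n per group = 2 × (1.960 + 0.842)² × 1081.1 / 16² = 66.3, so 67 (134 in total). With the t distribution, 67 per group gives power 0.798 and 68 gives 0.804, so 68 per group and 136 in total are reproduced. Inflation: 136 / (1 − 0.20) = 170.

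**2. Who is removed.** 0.20 × 170 = 34, leaving 136. With one outcome and one baseline covariate, pair-wise deletion means dropping the patient at that time point. A patient lost only between t2 and t3 stays in the t2 comparison, so 34 is an upper figure at t2 under the planned rate. At t3 that patient is dropped and the observed t2 value goes unused.

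**3. When deletion does no harm.** Complete-case ANCOVA was simulated with 85 per arm, about 20% drop-out, a true effect of zero and 4000 runs per scenario.

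| Assumed drop-out mechanism | Mean estimate (ms) | Type I error |
|---|---|---|
| MCAR | −0.04 | 5.1% |
| Depends on baseline only | 0.09 | 4.7% |
| Depends on outcome, equally in both arms | −0.12 | 5.1% |
| Depends on outcome in the intervention arm only | −4.3 | 12.8% |

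Negative values favour the intervention. Only the last scenario shows material bias: 4.3 / 16 = 27% of the target difference.

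**4. A worked NMAR illustration.** Assume that intervention completers gain 16 ms, intervention drop-outs gain nothing, and control drop-outs resemble control completers. With drop-out proportion p, the all-randomised effect is 16 × (1 − p), while deletion reports 16.

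| p | All-randomised effect (ms) | Deletion (ms) | Overstatement |
|---|---|---|---|
| 0.10 | 14.4 | 16 | 1.6 / 14.4 = 11% |
| 0.20 | 12.8 | 16 | 3.2 / 12.8 = 25% |
| 0.30 | 11.2 | 16 | 4.8 / 11.2 = 43% |

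**5. Would imputation under MAR correct this?** No. Imputing by arm fills in intervention drop-outs from intervention completers, so at p = 0.20 the expected result is 0.80 × 16 + 0.20 × 16 = 16 ms, the same as deletion. A delta-adjusted analysis lets the imputed drop-outs do worse. With their gain lowered by the full 16 ms, it gives 0.80 × 16 + 0.20 × 0 = 12.8 ms.

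**The case against.** The strongest reply is that deletion may cost little here, and that several tempting stronger readings go beyond the document.

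- **A reader might infer that the effect is biased.** The document does not show this. Three of the four simulated mechanisms gave no material bias, and the fourth is an assumption. The article offers no drop-out rates by arm or reasons for loss.
- **A reader might infer that the 3.2 ms gap is the price of deletion compared with imputation.** It is not. Step 5 shows that an MAR analysis shares it. Other variables help only where they are observed and predict the missing value, and patients lost before t2 will usually lack t3 too.
- **A reader might infer that the whole primary analysis is complete-case.** Other values judged MCAR or MAR are still multiply imputed.
- **A reader might equate stopping the training with deletion.** The Monitoring section distinguishes discontinuing the assessment from discontinuing the intervention. Someone who stops training but attends the test has an outcome and is analysed as randomised.
- **A reader might infer a loss of power.** The sample size already allows for 20% drop-out.

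It is also fair that a condensed article need not list imputation variables. All of this stands, and it limits the size of the claim. It does not rescue the rule. The article states the deletion of drop-outs expressly; it is not a detail left out. The planned drop-out comparisons describe who was lost but correct nothing.

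**Conclusion.** The rule is wrong as written. It excludes drop-outs (up to 34 of 170 at the planned rate) from an analysis described as intention to treat, collides with the imputation sentence before it when drop-out is MAR, ignores t2 information at t3, and turns on a distinction that the data cannot make.

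The bias is conditional. It arises if missingness relates to outcome differently by arm, and is not material if drop-out is MCAR, baseline-dependent or symmetric. The 12.8 versus 16 ms example and the 4.3 ms simulation result rest on assumed NMAR mechanisms. They show why an NMAR sensitivity analysis is needed for the primary endpoint. They do not measure a benefit of imputation over deletion. What the MAR analysis gains is consistency with the stated principle, a fixed analysed set, and use of the t2 value at t3.

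**What to change.** 1. Delete the pair-wise-deletion sentence, and the provision that lets an analysis of the missing data choose the method.
2. State that the primary analysis includes every randomised patient, drop-outs included, under MAR. Use either multiple imputation by arm with baseline and the other follow-up value, or one repeated-measures model for t2 and t3.
3. Add a delta-adjusted (tipping-point) sensitivity analysis for NMAR drop-out in the primary endpoint.
4. Keep the complete-case ANCOVA as a sensitivity analysis only.

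The cost is one paragraph of protocol or analysis-plan wording and a little programming. No extra data are needed and the sample size stays at 170. The change should be fixed and dated before the outcome data are analysed.

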#### Main research question

The primary and secondary endpoints will be analyzed according to the intention-to-treat principle. Treatment effects (between-group effects) will be calculated separately for each follow-up time point using analysis of covariance (ANCOVA) adjusting for baseline values. Statistical significance (*p* < 0.05, two-sided), difference in means with 95% confidence intervals (CI), and effect sizes (ή^2^) will be reported for all outcomes. Furthermore, within-group effects, including standardized effect sizes (SES) and accompanying 95% CI, will be calculated for both study groups. Bonferroni corrections to adjust the significance level for multiple tests are planned within secondary cognitive outcomes. Further secondary outcomes will be analyzed exploratorily without adjustment. A sensitivity analysis is conducted for primary analysis by additionally including the group as random effects in a linear mixed model for the primary endpoint to estimate the effect of the group.

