### Study setting and participants

The study is performed at the University Hospital Würzburg, Comprehensive Cancer Center Mainfranken (CCCMF), Germany. The university hospital is a certified cancer center for the types of tumors included.

The inclusion criteria are (i) a curative tumor diagnosis (breast cancer, blood cancer, gastrointestinal tumors, malignant melanoma), (ii) after chemotherapy, radiation therapy, after or ongoing antibody therapy, (iii) age between 18 and 79 years, (iv) and self-reported cognitive impairment with onset temporally related to cancer diagnosis (FACT-COG PCI18, cut-off score ≤ 55 [20, 21]).

The exclusion criteria are a lack of German language abilities or language disorders, severe cognitive impairment such as dementia, brain tumors/central nervous system cancer, immobility or non-resilience of the patient, and a palliative state.

Furthermore, eligible patients must have access to a terminal device with Internet access and must provide written informed consent. Assessment of exclusion criteria is detailed in Supplementary material 1.

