t1 indicates before intervention; t2, after 3 months; t3, after 6 months. To objectify cognitive performance decline (cognitive fatigability), the TAP subtest alertness was repeated at the end of the test battery to measure

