#### Primary and secondary outcome measure

##### TAP [25, 26]

The TAP provides a computer-based battery of different tests that can be used to assess the various aspects of attention in a differentiated way. Detailed information is available at https://www.psytest.net/en/test-batteries/tap/subtests. Norm values (i.e., age-, gender-, and education-corrected T-scores) are provided for all subtests. These are used for the analyses.

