##### TAP—alertness

Alertness refers to the condition of general wakefulness that enables a person to respond quickly and appropriately to any given demand. It is the pre-requisite for effective behavior, and is in this respect the basis of every attention performance [25, 26]. The test examines reaction time under two conditions: In the first condition, intrinsic alertness (primary outcome) is measured by a visual stimulus that appears on the monitor at a randomly varying interval. The subject should respond as quickly as possible by pressing a key (“tonic arousal”). In the second condition, “phasic arousal” or temporal orientation of attentional focus is measured in response to the same visual stimulus preceded by a cue stimulus presented as a warning tone. Reaction time in milliseconds (mean, standard deviation (SD)) and norm-values are available, respectively.

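### The primary ANCOVA adjusts only for the outcome's own t1 value; pre-specifying other prognostic t1 data would be a cheap, probably modest gain in precision, once the ms versus T-score conflict is settled

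*Protocol article*

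**What the plan says.** All references are to the protocol article.

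- **Model.** Statistical analysis, Main research question: "Treatment effects (between-group effects) will be calculated separately for each follow-up time point using analysis of covariance (ANCOVA) adjusting for baseline values". No other covariate is named. The only variant is a sensitivity mixed model that adds group as a random effect.
- **Sample size.** The calculation takes R² = 0.5 "for the regression of the response on only the baseline covariate", and "a mean difference of 16 ms (SD = 46.5) between the intervention and control group was estimated". With two-sided α = 0.05 and 80% power this leads to 136 evaluable patients (68 per group), and to 170 after allowing for 20% dropout.
- **Scale.** Outcomes and measurements, and Sample size, define the primary outcome as intrinsic-alertness reaction time in milliseconds. The TAP section says: "Norm values (i.e., age-, gender-, and education-corrected T-scores) are provided for all subtests". Its next sentence states that the analyses use these values.
- **Other t1 information.** Eligible patients are "age between 18 and 79 years". Sociodemographic and medical data are collected, though the items are not listed. In the second condition of the alertness subtest, "temporal orientation of attentional focus is measured in response to the same visual stimulus preceded by a cue stimulus". The footnote to Table 2 adds that "the TAP subtest alertness was repeated at the end of the test battery".
- **Timing.** Under Randomization and allocation concealment, patients are allocated only after the t1 assessment is complete, so all t1 values precede allocation.

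**The concern.** Pre-specified baseline covariates that predict the outcome narrow the confidence interval for the treatment effect in a randomised trial without introducing bias. The protocol points to such predictors itself. The test norms correct for age, gender and education, the age range spans six decades, and the t1 session yields further reaction times. A single t1 run carries measurement error and need not contain all of this information.

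The calculation has no margin beyond the dropout allowance: one evaluable patient fewer per group takes power just below 80%. A small gain in precision is therefore worth having if it costs almost nothing.

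**Working it through.** **Inputs from the document.** Difference δ = 16 ms; SD σ = 46.5 ms; R² = 0.5; two-sided α = 0.05; n = 68 per group (Sample size).

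**Step 1: reproduce the plan's figure.**
- Residual SD = σ√(1 − R²) = 46.5 × √0.5 = 32.88 ms.
- SE of the difference = 32.88 × √(2/68) = 5.64 ms.
- Noncentrality = 16 / 5.64 = 2.84, with 136 − 2 − 1 = 133 degrees of freedom.
- Noncentral-t power: 80.4% at 68 per group, 79.8% at 67, 79.2% at 66. The smallest n reaching 80% is 68, so 136 in total.
- 136 / (1 − 0.20) = 170.

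The stated numbers reproduce, and the planned model delivers the planned power.

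**Step 2: the worst case of adding terms.** If the additional covariates explain nothing (R² stays 0.5), power with five covariates in total is 80.4%. The cost in degrees of freedom is negligible.

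**Step 3: the possible gain on the ms scale.** The correlations are not in the document, so these are assumptions:
- t1 with t2 intrinsic reaction time: r₁ = √0.5 = 0.707, which follows from the stated R²;
- age with every reaction time: 0.3 to 0.5;
- a second t1 reaction time (phasic or end-of-battery) with the t2 outcome: 0.60 to 0.70; with t1 intrinsic reaction time: 0.7 to 0.8.

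With one added covariate that correlates r₂ with the outcome and r₁₂ with the t1 value:

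R² = (r₁² + r₂² − 2 r₁ r₂ r₁₂) / (1 − r₁₂²)

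*Age alone*
- Correlation 0.3: (0.5 + 0.09 − 2 × 0.707 × 0.09) / 0.91 = 0.508, power 81.1%.
- Correlation 0.5: (0.5 + 0.25 − 2 × 0.707 × 0.25) / 0.75 = 0.529, power about 82.7%.

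*A second t1 reaction time alone*
- r₂ = 0.60, r₁₂ = 0.80: (0.5 + 0.36 − 2 × 0.707 × 0.48) / 0.36 = 0.503, power 80.7%.
- r₂ = 0.70, r₁₂ = 0.70: (0.5 + 0.49 − 2 × 0.707 × 0.49) / 0.51 = 0.582, power 86.9%.
- Just outside the assumed range the gain vanishes. When r₂ = r₁ × r₁₂, for example 0.707 × 0.80 = 0.566, R² stays at 0.500.

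*Age plus a second t1 reaction time* (three predictors, R² = r′C⁻¹r, where r holds the correlations with the outcome and C those among the predictors)

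| | R² | SE relative to plan, √((1 − R²)/0.5) | Equivalent extra evaluable patients, 136 × (0.5/(1 − R²) − 1) | Power, 68 per group |
|---|---|---|---|---|
| Low corner | 0.511 | 0.989 | about 3 | about 81% |
| High corner | 0.593 | 0.902 | about 31 | about 88% |

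The high corner needs the second reaction time to predict the t2 outcome at 0.70, almost as well as the t1 value of the outcome itself (0.707), while correlating only 0.7 with that value, and also an age correlation of 0.5.

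**Step 4: the T-score scale.** If the TAP section governs, age, gender and education have already been taken out of the score, and putting them in the model again would add little. Only the phasic or end-of-battery measure remains. If the correlations assumed above carried over, its range would be that of the second reaction time alone: 80.7% to 86.9%, with zero gain also possible.

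**The case against.** The strongest reply is that nothing here is wrong. Baseline-adjusted ANCOVA is valid, the trial was sized on exactly that model, and the planned power is delivered. This stands. A reader might infer from the thin margin that the trial is underpowered, or that unadjusted age or education biases the result. The document supports neither: the arithmetic reproduces, and randomisation deals with chance imbalance without bias in a baseline-only model.

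A reader might also infer that age, gender and education are plainly left unused. That holds only on the ms scale, because the protocol also says that corrected T-scores are analysed. Education, moreover, is not named as a collected item. It is only suggested by the general mention of sociodemographic data and by the norms.

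Third, the gain rests wholly on assumed correlations. The phasic condition is described as measuring something different from intrinsic alertness, and the end-of-battery repeat is meant to capture fatigability, so neither need add much. This stands too, and 88% should not be read as an expectation.

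Fourth, the change comes late. Trial status puts the end of recruitment at June 2025, the article appeared in October 2025, and follow-up assessors are not blinded. A new primary model could look chosen after the fact. This is a real cost, but not decisive: the analysis is assigned to a research assistant at the biometry institute, so the list can still be fixed and dated before that person sees outcomes by arm.

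**Conclusion.** The point holds as a low-cost improvement, not as an error. The primary model uses one covariate where other prognostic t1 data exist. The likely gain is modest: from 80.4% to about 81–83% with age on the ms scale, and to about 81–88% with age plus a second t1 reaction time, the upper end being a best case. A second reaction time alone may add nothing. The downside is close to nil (80.4% if the extra terms are pure noise). These ranges rest on the stated R² of 0.5 and on correlations that the document does not give. Which covariates are worth adding depends on whether the primary analysis is in ms or in T-scores, and on this the protocol contradicts itself.

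**What to change.** 1. Reconcile the scale first. State under Main research question whether the primary ANCOVA uses intrinsic reaction time in ms or the T-score, and align the TAP section with it.
2. If ms: pre-specify t2 intrinsic reaction time ~ arm + t1 intrinsic reaction time + age + gender + education (if collected), optionally + t1 phasic reaction time.
3. If T-scores: leave out age, gender and education; consider only one second t1 reaction time (phasic or end-of-battery).
4. Fix and date the list before the analysing statistician sees outcomes by arm. Report the baseline-only ANCOVA as a supporting analysis, which keeps the link to the sample size calculation.
5. For TMT times and 6MWT metres, if analysed as raw scores, age and gender may be added in the same way.

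The cost is wording, a few of the 133 residual degrees of freedom, and a documented departure from the published model late in the trial. No new data or patients are needed.

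### The 80% power stated for d = 0.48 on secondary outcomes is at uncorrected p < 0.05, so it does not describe the Bonferroni-corrected secondary cognitive outcomes

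*Protocol article*

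**What the plan says.** The Protocol article, section Sample size, derives the trial size from the primary outcome: "Thus, a total of *n* = 136 persons (*n* = 68 per group) is required". It then extends the claim to the secondary outcomes as a whole: "medium between-group effects (*d* = 0.48) on secondary outcomes can be detected", at p < 0.05 and 80% power. It adds that power may be insufficient for smaller effects, and for that reason promises effect sizes with 95% confidence intervals.

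Under Statistical analysis, subsection Main research question, every endpoint is tested by baseline-adjusted ANCOVA, separately at t2 and t3. On multiplicity, "Bonferroni corrections to adjust the significance level for multiple tests are planned within secondary cognitive outcomes"; the remaining secondary outcomes are exploratory and unadjusted. The number of tests in the corrected family is not given. Nor does the article say whether the d of 0.48 is in units of the raw SD or of the SD left after baseline adjustment.

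**The concern.** The power sentence and the testing rule use different significance levels for the same outcomes. The secondary cognitive outcomes will be judged at 0.05/m, yet the detectable effect quoted for them is at 0.05. The warning about smaller effects does not close this gap, because it leaves d = 0.48 itself looking safe.

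These outcomes include verbal and working memory, which a memory training is meant to improve. A reader who takes the power to be 80% may treat a non-significant corrected result as evidence that no medium effect exists, when the test may have had clearly less power than that.

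**Working it through.** **Inputs.** From Sample size: 68 evaluable per group, d = 0.48, p < 0.05, and R² = 0.5 for the baseline covariate (primary outcome only). From Main research question: two-sided tests, ANCOVA and Bonferroni. Not in the article, hence assumed: m, the scale of d, and R² for the secondary outcomes.

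**Step 1: reproduce the stated figure.** Noncentrality = d × √(n/2) = 0.48 × √34 = 2.80. The two-sided 5% critical t with 133 df is 1.978. Power = 79.4% (79.9% with the normal approximation). The effect detectable with 80% power is 0.484 (0.480 normal). The stated figure is right at alpha = 0.05.

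**Step 2: possible family sizes.** These are counts from the article's lists, not stated values of m.
- m = 5: the non-primary cognitive test rows of Table 2.
- m = 9: Go/Nogo time and mistakes (2), working memory (1), VLMT scores (4), TMT-A and TMT-B (2).
- m = 13: those nine plus the four FACT-Cog scales.
- m = 26: those thirteen at both t2 and t3.

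**Step 3: power at d = 0.48 with alpha = 0.05/m.** If d is already on the baseline-adjusted scale, the noncentrality stays at 2.80. If d is in raw SD units, it becomes 0.48/√(1 − R²) × √34, which is 3.96 at R² = 0.5 and 3.35 at an assumed R² = 0.3.

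| m | alpha | critical t | d baseline-adjusted | d raw, R² = 0.5 | d raw, R² = 0.3 |
|---|---|---|---|---|---|
| 1 | 0.05 | 1.978 | 79.4% | 97.6% | 91.3% |
| 5 | 0.01 | 2.613 | 57.5% | 90.9% | 76.7% |
| 9 | 0.0056 | 2.819 | 49.4% | 87.0% | 70.0% |
| 13 | 0.0038 | 2.942 | 44.6% | 84.3% | 65.6% |
| 26 | 0.0019 | 3.165 | 36.2% | 78.4% | 57.3% |

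**Step 4: effect detectable with 80% power.** With d on the baseline-adjusted scale, it is 0.484 at m = 1, 0.594 at m = 5, 0.629 at m = 9, 0.650 at m = 13 and 0.689 at m = 26. The rise is 0.594/0.484 = 1.23 to 0.689/0.484 = 1.42, so 23% to 42%. The ratio is the same on the raw scale, because both values are multiplied by √(1 − R²).

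**Step 5: what would restore 80% at a raw d of 0.48.** R² = 1 − (0.48/detectable d)². For m = 5 this is 1 − (0.48/0.594)², about 0.35. It is about 0.42 for m = 9 and 0.51 for m = 26.

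**Step 6: which scale is meant.** The value 0.48 matches a plain two-sample calculation with no baseline gain (0.480 to 0.484). It is also close to the primary effect on the residual scale, 16/(46.5 × √0.5) = 0.487. The raw primary effect is 16/46.5 = 0.344. The figures alone do not settle the question.

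**Step 7: Holm against Bonferroni.** Simulation with 200,000 runs, normal tests, correlation 0 or 0.5, and d = 0.48 on the baseline-adjusted scale. Average power per real effect:
- All effects real: from 59% to 69–70% at m = 5, and from 47% to 58% at m = 12.
- About half real: a gain of 2 to 3 points.
- One real: a gain of 0.2 points or less.

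Simulated family-wise error under Holm was at most 4.7%.

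**The case against.** The power sentence names its own alpha and is correct at that alpha. It stays correct for the unadjusted secondary outcomes: fatigue, quality of life, depression and anxiety. The family definition may stand in an analysis plan or full protocol that is not shown, so its absence here is not in itself a fault. The promised effect sizes and confidence intervals give some protection against reading non-significance as no effect. Bonferroni is valid and prespecified. All of this stands. It narrows the point to one of scope: the sentence covers secondary outcomes in general and excepts none.

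A reader might infer that power for the secondary cognitive outcomes simply is 36% to 58%. The article does not support that. The range needs a family of 5 to 26 tests, which is not stated, and a d that already includes the gain from baseline adjustment, which is not stated either. If d is in raw units and the R² of 0.5 carried over, power would remain above 80% for 13 tests and be 78% for 26. But that R² is assumed only for the primary reaction time; none is given for memory, trail-making or error scores. Neither reading is established.

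A reader might also infer an arithmetic error or a flaw in the trial's size. There is neither: the 80% reproduces, and the primary sample size is untouched.

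**Conclusion.** The point holds as a mismatch between the stated power and the planned tests. The 80% at d = 0.48 applies to the secondary outcomes analysed without adjustment, and not to the Bonferroni-corrected cognitive ones. Whatever the scale of d, correction for 5 to 26 tests raises the detectable effect by about 23% to 42% over its uncorrected value, and the Sample size section does not reflect this.

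Whether power at d = 0.48 actually falls below 80% depends on m, the scale of d and the baseline correlation of each secondary outcome. On the baseline-adjusted reading the shortfall is large even for five tests. On the raw reading, baseline adjustment may offset part or all of it.

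**What to change.** 1. In Sample size, restrict the 80% statement for d = 0.48 to the secondary outcomes analysed without adjustment.
2. Add the effect detectable with 80% power at 0.05/m for the secondary cognitive outcomes, stating m, the scale of d and any R² relied on. For nine tests and d on the baseline-adjusted scale this would be about 0.63.
3. Replace Bonferroni with Holm within that family. It has the same family-wise error control under any dependence and never rejects less. This is an improvement, not the repair of an error, and its gain depends on how many effects are real: about 10 to 12 points if all are (5 to 12 tests), 2 to 3 if half are, near zero if only one is.

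The cost is wording and one recalculated figure; recruitment and conduct do not change. The published detectable effect becomes less favourable, and simultaneous confidence intervals that match Holm are less simple than those for Bonferroni. The planned 95% intervals are not described as adjusted, so they need not change.
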